#### Criteria for discontinuing or modifying allocated interventions {11b}

Use of study drug will be halted or modified if any of the following criteria develop:
Severe gastrointestinal symptoms prevented oral administration of the trial drug.Respiratory compromise: dyspnea, wheezing, stridor, hypoxemia.A decrease in systolic blood pressure to < 90 mmHg or > 30% decrease from baseline or a diastolic drop of > 30% from baseline.Tachycardia with an increase in resting heart rate to > 130 bpm; or bradycardia < 40 that is associated with dizziness, nausea, or feeling faint.Syncope.Confusion.Any other symptom or sign which, in the investigators’ judgment, requires withdrawal of the subject from the study warrants halting the oral administration.

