### Outcomes measurements {12}

#### Primary outcome measure

The primary outcome is proportion of clinical improvement within 7 days. And clinical improvement is defined as at least one of the following criteria: (i) 3 points or less in the 7-category ordinal scale; (ii) National Early Warning Score 2 (NEWS2) of ≤2 and maintained for 24 h [23]. Seven-category ordinal scale was used in other influenza study [24–27]. The seven-category ordinal scale consisted of the following categories: 1, not hospitalized with resumption of normal activities; 2, not hospitalized, but unable to resume normal activities; 3, hospitalized, not requiring supplemental oxygen; 4, hospitalized, requiring supplemental oxygen; 5, hospitalized, requiring nasal high-flow oxygen therapy, noninvasive mechanical ventilation, or both; 6, hospitalized, requiring ECMO, invasive mechanical ventilation, or both; and 7, death. The UK’s National Early Warning Score 2 have good predictive abilities in patients with infections and sepsis [23], which are detailed in the Table 1.

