### Sample size {14}

Sample size calculations are based on the primary endpoint (the proportion of clinical improvement within 7 days after randomization). At the 5% significance level, a total of 101 patients per group is required to achieve 90% power and to determine an increase of 20% in the proportion of clinical improvement between *QZQG* group and the placebo group, assuming that the clinical improvement rate within 7 days after randomization of the placebo group receiving oseltamivir plus routine symptomatic treatment is about 50%. With an estimated dropout rate of 10–20%, a total of 228 patients are planned to be enrolled. If the initial hypothesis is not rejected, subsequent comparison is considered exploratory, and no conclusion is made.

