## Statistical methods

### Statistical methods for analyzing primary and secondary outcomes {20a}

The primary study analysis will occur when the last patient has either withdrawn or completed day 28 visit, and will be based on cleaned data for all patients up to and including this point. The clinical data will be managed and analyzed by the independent statisticians from a third party (School of Public Health, Fudan University,) in accordance with the statistical analysis plan. Data management and analysis will use SAS V.9.4 (SAS Institute, Cary, NC, USA).

All statistical inferences will be determined using two-sided tests. *P* < 0.05 will be considered significant, and 95% confidence intervals will be used. Data will be described as the mean, standard deviation, and confidence intervals. If necessary, minimum, maximum, P25, P75, and median values will be provided. Paired measurement data will also show the differences between the mean and standard deviation. When using nonparametric methods, median and mean values will be provided. Count data will be described using the frequency distribution and corresponding proportion. Qualitative information will be described using the positive rate, the number of positive cases, and the denominator.

Baseline data analyses (in FAS and PPS) will include demographic indicators and primary and secondary outcomes before intervention. Measurement data will be described using a *t*-test or *t*’ test (if the variance is absent). Count data will be described using the Pearson’s *χ*^2^ test. Rating data will be described using the two-sample Wilcoxon rank sum test.

Logistic regression model will be used to explore the efficacy (*QZQG* group and placebo group) and factors affecting efficacy. Dependent variable is the proportion of clinical improvement at day 7. In addition to drugs, independent variables also include the basic information and life behavior factors of participants. The basic information includes gender, height, weight, age, and underlying diseases that include chronic obstructive pulmonary disease, asthma, diabetes, hypertension, hyperlipidemia, hyperuricemia, cardiovascular disease, autonomic nervous dysfunction, lung cancer, other tumors, etc. Life behavior factors mainly include smoking and drinking.

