### Definition of analysis population relating to protocol nonadherence {20c}

The intent-to-treat (ITT) population is defined as all randomized patients, whether or not the patient received the assigned treatment. The ITT patients will be analyzed according to the treatment assigned at randomization. The ITT population includes the patients who agree to enroll in the study and sign an informed consent form. However, ITT population involves those who have never received study drugs or never completed observation records. Efficacy analyses will be conducted for the modified intent-to-treat (mITT) population. This is defined as all patients randomized who received at least one dose of *QZQG* formula and were centrally assessed as RT-PCR positive for influenza at any timepoint, with patients grouped according to the treatment assigned at randomization. The per-protocol set is used to analyze the main outcome for evaluating efficacy and to examine the consistency of the results from the mITT. The PPS is defined as follows: (1) full compliance with inclusion and exclusion criteria; (2) the compliance of medication consumption is over 80%; (3) the patients complete the test and record of the outcome and safety evaluation at every time node; and (4) completion of the clinical trial without major protocol violation. The safety analysis set (SAS) is defined as patients who received any amount of study treatment. Patients will be analyzed according to the treatment received. Patients who were randomized to the study but who did not receive any study drug will not be included in the safety population. The SAS will be used for the analysis of all safety indicators. Multiple imputation will be used for missing data.

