	Adverse events are definitely caused by the disease or the main cause of the disease

Participants may experience exacerbations due to natural disease progression, poor drug efficacy, or other reasons, including but not limited to respiratory failure, acute necrotizing encephalopathy, shock, multiple organ dysfunction, and other conditions that require clinical monitoring. If the participant is judged to be critically ill in the process of trial, the research doctor at the center where the participant is located should report to the sponsor and the ethics committee within 24 h. The trial drug intervention should be stopped at the same time. The research doctor should immediately initiate a clinical treatment regimen on severe clinical situation. When necessary, the sponsoring unit and the project funding department will organize multidisciplinary consultations and propose a comprehensive clinical treatment plan. The branch center and the sponsor are jointly responsible for the treatment, follow-up monitoring, and follow-up of critically ill participants.

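### Multiple imputation is applied whatever the reason for loss, so a patient who leaves unimproved for an adverse event or deterioration, with no later data, can be counted as improved

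*Protocol article*

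**What the plan says.** All references are to the Protocol article.

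- **Missing data ({20c}):** "Multiple imputation will be used for missing data". The sentence is unqualified. It names no exception by reason for loss, no failure rule and no sensitivity analysis.
- **Endpoint (Primary outcome measure):** "The primary outcome is proportion of clinical improvement within 7 days". A patient qualifies with an ordinal score of 3 or less, or with NEWS2 of 2 or less held for 24 h. The ordinal scale ends with "invasive mechanical ventilation, or both; and 7, death", so escalation and death are observed values.
- **Exits:** Most items in {11b} only halt or modify study drug. The last is a catch-all for any sign or symptom that, in the investigator's judgment, "requires withdrawal of the subject from the study warrants halting the oral administration". Assessment of adverse events adds that if a mild or moderate event does not improve with treatment or a reduced dose, the doctor reports it and terminates the trial, presumably for that patient.
- **Critical illness (same section):** "The trial drug intervention should be stopped at the same time", but the centre and sponsor remain responsible for follow-up.
- **Timing of the analysis ({20a}):** "The primary study analysis will occur when the last patient has either withdrawn or completed day 28 visit".
- **Consistency check ({20c}):** the per-protocol set requires complete outcome records and completion of the trial.

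**The concern.** The primary endpoint is a proportion of successes, and a patient who improved before leaving is already a known success. Among patients with unknown status, those who left because of a reaction or worsening are more likely than average to be failures. A rule that imputes all of them, whatever the reason, gives some of these failures the status of improved.

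The two stated efficacy analyses do not guard against this: the modified intention-to-treat analysis imputes these patients and the per-protocol analysis removes them. No stated analysis counts them as not improved. If one arm loses more patients for such reasons, the comparison is tilted towards that arm.

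**Working it through.** **Inputs from Sample size {14}:** 50% improvement on placebo, a 20-point target, 228 patients (114 per arm), 10–20% dropout. That is 114 × 0.10 = 11.4 to 114 × 0.20 = 22.8 patients per arm. The split of losses between arms and the outcomes of those lost are not given, so they are assumptions below. Using all 114 randomised per arm is a simplification, because the efficacy set is smaller.

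**The plan's own figure.** The article says: "At the 5% significance level, a total of 101 patients per group is required to achieve 90% power". The pooled normal formula for 50% vs 70% is n = [z_α√(2·0.6·0.4) + z_β√(0.5·0.5 + 0.7·0.3)]² / 0.20².
- One-sided 5%: (1.645·0.6928 + 1.2816·0.6782)² / 0.04 = 101, as stated.
- Two-sided: (1.960·0.6928 + 1.2816·0.6782)² / 0.04 = 124.

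Since {20a} says "All statistical inferences will be determined using two-sided tests", that mismatch is a separate matter. The calculations below are two-sided.

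**Bias formula.** Let d be the fraction lost in an arm, q the true improvement rate of those lost and m their mean imputed probability. The arm's rate is then overstated by d(m − q). The bias in the difference is this quantity for QZQG minus that for placebo.

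**Case A: no true effect (50% in both arms), all lost patients are failures (q = 0), m equal to the completers' rate 0.50/(1 − d).**

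| Loss QZQG / placebo | Imputed rates | False difference |
|---|---|---|
| 10% / 10% | 55.6% / 55.6% | 0 |
| 20% / 20% | 62.5% / 62.5% | 0 |
| 15% / 10% | 58.8% / 55.6% | +3.3 points |
| 20% / 10% | 62.5% / 55.6% | +6.9 points |
| 10% / 20% | 55.6% / 62.5% | −6.9 points |

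Type I error: imputation that uses no post-baseline information has about the precision of the completers alone.
- 20% / 10% (91.2 and 102.6 observed): SE = √(0.625·0.375/91.2 + 0.5556·0.4444/102.6) = 0.0705, and 0.0694/0.0705 = 0.98. The two-sided rejection probability at 1.96 is 0.166.
- 15% / 10% (96.9 and 102.6 observed): SE = √(0.5882·0.4118/96.9 + 0.5556·0.4444/102.6) = 0.0700, and 0.0327/0.0700 = 0.47. The rejection probability is 0.075.

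**Case B: completers improve at 70% (QZQG) and 50% (placebo), all lost patients are failures.** Imputation at these rates keeps the difference at 20 points.
- Equal 10% loss: the true rates are 0.9·70 = 63% and 0.9·50 = 45%, a difference of 18 points.
- Equal 20% loss: 56% and 40%, a difference of 16 points.
- 20% on QZQG, 10% on placebo: 56% and 45%, a difference of 11 points.

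The overstatement is 2, 4 and 9 points. The false improvers number 8.0 + 5.7 ≈ 14 of 228 at 10% loss in both arms, and 16.0 + 11.4 ≈ 27 at 20%.

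**How the size depends on the model.** With q = 0 the bias is proportional to m. Halving m in both arms halves the 6.9 points to about 3.5. A model that uses NEWS2 and ordinal scores recorded before withdrawal would lower m for a deteriorating patient.

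**The case against.** The strongest reply is that this is a condensed article which refers to an analysis plan not shown, and that the imputation model and its sensitivity analyses commonly belong there. That stands for the details of the model. It does not remove the point that the rule the article does state, for the primary endpoint, is unqualified.

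A reader might infer more than the documents support:
- **That patients leave mainly because they deteriorate or react.** No frequencies by reason are given. {18b} allows voluntary withdrawal for any reason, and the 10–20% dropout is not attributed to a cause.
- **That everyone who stops drug is imputed.** Most {11b} items halt or modify drug only. Participants are inpatients with vital signs scheduled through days 1–7, the critically ill are followed, and escalation and death are scored. The {20a} sentence sets the time of the analysis. It does not say that data collection ends with drug.
- **That those lost are imputed at the completers' rate.** Multiple imputation under missing at random assumes similarity given the observed data in the model. The completers' rate follows only if the model holds nothing informative.
- **That every early leaver is a failure.** Improvement counts at any time within 7 days, and a hospitalised patient without oxygen already meets the criterion. Someone withdrawn on day 3 may be an observed improver.

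Patients unblinded in an emergency are excluded under the allocation section {16a–16c}. That is also an outcome-related loss, but it happens by exclusion and is a different issue. Finally, counting adverse-event exits as failures is one choice of estimand. Imputation with sensitivity analysis is another accepted one.

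**Conclusion.** The point holds in a limited form. The stated rule ignores the reason for loss, some stated exits are related to outcome, and no stated analysis counts such an exit before improvement as a failure. It affects only patients who had not met the criterion and whose later status is truly unrecorded.

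The size cannot be fixed from the document. The 6.9 points and 17% type I error need three assumptions together: every dropout a failure, twice the loss on QZQG, and uninformative imputation. At 15% versus 10% loss, with the other two kept, the figures are 3.3 points and about 7.5%. Equal loss without a true effect leaves the difference unbiased, and the reverse imbalance works against QZQG. A reader might infer that the plan makes a poorly tolerated treatment look better or runs at 17% type I error. The documents show only that this could happen under those assumptions. This is a worthwhile, cheap improvement, not an error that must be corrected before the trial can be relied on.

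**What to change.** 1. **Outcome assessment.** Reconcile the last item of {11b} and the adverse-event termination sentence with the follow-up provided for critically ill patients, so that stopping study drug does not end outcome assessment unless the patient withdraws consent to follow-up. Use all observed status up to day 7 and keep the endpoint as improvement within 7 days. No change to when drug is stopped is proposed.
2. **Missing-data rule in {20c}, primary endpoint.** Count as not improved any patient who had not met the criterion and who died, or who left for deterioration, an adverse event or lack of efficacy without later data. Keep multiple imputation for other losses, with post-baseline NEWS2 and ordinal scores in the model.
3. **Sensitivity.** Add a tipping-point analysis that varies the imputed improvement rates by arm.

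The cost is wording in the protocol and analysis plan, settled before unblinding. Patients are inpatients and the visits already exist. Stated improvement rates will be slightly lower. At the outside, if every loss were such an exit and completers improved at 70% versus 50%, the analysed difference at 114 per arm would be 18 points with 78% power (10% loss in both arms) or 16 points with 68% power (20% loss). That reflects the smaller true effect in this scenario.

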## Monitoring

### Description of the data monitoring committee {21a}

The independent Data Monitoring Committee (DMC) DMC is responsible for reviewing the reports regarding protocol adherence and making recommendations to continue or terminate the study. The DMC members are all independent of the sponsor/funders and have no financial or other conflicts of interest.

### Harms {22}

#### Safety assessment

The dosage of *QZQG* formula used in this trial is within the recommended range based on the People’s Republic of China Pharmacopeia (2020 edition). To our knowledge, no serious adverse events of this formula have been reported so far. Considering that TCM may cause allergic reactions and gastrointestinal reactions (nausea, vomiting, diarrhea, etc.), it is necessary to arrange clinical tests to evaluate the safety of the formula and protect the participants. Safety is evaluated by using vital signs, cardiopulmonary signs, electrocardiography, chest radiograph, laboratory tests, and adverse events. Vital signs include height, weight, heart rate, blood pressure, and finger pulse oxygen saturation. Laboratory tests include blood routine test, liver and kidney function, electrolyte test, arterial blood gas analysis, bleeding and coagulation function, and myocardial enzyme. The abovementioned and other unmentioned laboratory tests need to be arranged flexibly according to the condition of the participants. But the laboratory tests arranged at the planned visit are necessary.

#### Assessment of adverse events

Any adverse event that occurs to a participant will be recorded in the CRF regardless of relationship to the intervention. Adverse events are divided into three levels: mild, moderate and severe (Table 3). And the adverse events are not necessarily related to the drugs. Any cause-and-effect relationship between adverse events and the study drugs will be determined by the classifications as shown in Table 4. If patients with mild or moderate adverse events do not show significant improvement after medical treatment or drug reduction, the research doctors need to report to the ethics committee and terminate the trial. All serious adverse events will be reported within 24 h to the Principal Investigator, Steering Committee, IRB, the sponsor, and CFDA.

**Table 3 Tab3:** Classification of disease severity

Classification	Features
**1. Mild**	Participants can continue to participate in the trial without medical treatment and impact on the health.
**2. Moderate**	Participants could not tolerate the drug or need medical treatment. Such events partially affect the participants’ functional activity without threat to life safety.
**3. Severe**	The events pose threat the life of participants, leading to death or disability, which requires immediate withdrawal of medicine or emergency monitoring treatment.

**Table 4 Tab4:** Classification of the correlation between adverse events and drugs

Classification	Features
**1. Definite**	Use of the experimental drug has a definite relationship with time.
	The event is consistent with the known adverse reactions of Chinese herbal medicine.
	Adverse events disappear after drug withdrawal and reappear after repeated administration.
**2. Probable**	Use of the experimental drug has a reasonable relationship with time.
	Adverse events are partially in line with the known adverse reactions of Chinese herbal medicine.
	It is difficult to identify a cause owing to disease or other reasons.
**3. Possible**	Use of the experimental drug has a reasonable relationship with time.
	Adverse events do not conform to adverse reactions of Chinese herbal medicine.
	The adverse events are likely to be caused by diseases or other reasons.
**4. Remote**	There is a possible connection between time and experimental drug.
	It is easily explained and verified through the disease or other reasons.
**5. Unrelated**	There is no connection between time and the test drug.
	Adverse events are definitely caused by the disease or the main cause of the disease

Participants may experience exacerbations due to natural disease progression, poor drug efficacy, or other reasons, including but not limited to respiratory failure, acute necrotizing encephalopathy, shock, multiple organ dysfunction, and other conditions that require clinical monitoring. If the participant is judged to be critically ill in the process of trial, the research doctor at the center where the participant is located should report to the sponsor and the ethics committee within 24 h. The trial drug intervention should be stopped at the same time. The research doctor should immediately initiate a clinical treatment regimen on severe clinical situation. When necessary, the sponsoring unit and the project funding department will organize multidisciplinary consultations and propose a comprehensive clinical treatment plan. The branch center and the sponsor are jointly responsible for the treatment, follow-up monitoring, and follow-up of critically ill participants.

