### Plans to promote participant retention and complete follow-up {18b}

During the course of the study, participants may voluntarily withdraw from the trial for subjective or objective reasons at any time. When the subjects request to withdraw, the investigators at study sites must fully inform the importance of continuing to retain and complete the trial, including better observation of drug efficacy and potential adverse reactions, and providing more valuable data for follow-up studies.

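### For a mild or moderate adverse event that persists, the protocol orders more than stopping study drug, so a site could end that patient's observation

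*Protocol article*

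**What the plan says.** The rule stands in the protocol article under Harms {22}, Assessment of adverse events. It is triggered when a patient's mild or moderate event shows no significant improvement, and it reads: "after medical treatment or drug reduction, the research doctors need to report to the ethics committee and terminate the trial". The sentence does not say whether the study, the patient's participation or the study drug is meant. It also does not depend on the causality classes of Table 4, and the same paragraph notes that adverse events need not be drug-related.

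Four other provisions bear on it:

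- Table 3, severe events: "which requires immediate withdrawal of medicine or emergency monitoring treatment".
- The paragraph on critically ill participants after Table 4: "The trial drug intervention should be stopped at the same time". It then makes the branch centre and the sponsor jointly responsible for treatment and follow-up.
- Safety assessment: "TCM may cause allergic reactions and gastrointestinal reactions".
- Trial design {8} and Table 2: 7 days of intervention, then 21 days of observation with visits on days 14, 21 and 28. Adverse-event recording is marked at each of those visits.

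**The concern.** Stopping study drug for a moderate event that persists is reasonable clinical practice. Ending the patient's trial is a different act, because it can also end the collection of outcome and safety data. The rule uses the broader words for the lesser events, while the article uses plain drug-stopping words for worse ones.

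At stake is follow-up that depends on treatment. If herbal reactions persist more often on QZQG than on placebo, the rule would remove more observation from the QZQG arm. Part of what is removed would be the later course of the reactions that the safety analysis is meant to describe.

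**Working it through.** No sample size, power or event rate enters this point, and the plan gives no figure to reproduce. The check compares provisions and then counts what one affected patient can lose.

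**1. What each provision orders**

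| Situation | Action ordered | Follow-up stated there |
|---|---|---|
| Mild or moderate event, not improving | ethics report and termination of the trial | none |
| Severe event (Table 3) | withdrawal of medicine or emergency monitoring treatment | none |
| Critically ill participant | trial drug stopped | yes, assigned to branch centre and sponsor |
| Criteria in {11b} | drug halted or modified | none |

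The first row alone goes beyond the drug in its main instruction. The third row covers a different group, so it does not contradict the first. It shows that narrower wording was available in the same section. The {11b} list does not help a site to separate the two acts, because its last item itself joins them: "requires withdrawal of the subject from the study warrants halting the oral administration".

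**2. Which level is meant**

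The sentence is about patients with events, and the actors are research doctors. The retention section {18b} also speaks of completing the trial when it means one patient's participation. The patient-level reading is therefore the likely one.

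**3. What one patient can lose if observation ends during dosing**

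- Total period: 7 + 21 = 28 days. Post-treatment days lost: up to 21 of 28, which is 21/28 = 75%.
- Visits lost: days 14, 21 and 28, which is 3 of 3 observation visits.
- Secondary outcomes with a stated time frame beyond day 7: 4 to day 28 (complications, systemic antibiotics, length of stay, time on oxygen) and 2 to day 14 (symptom improvement, defervescence), so 4 + 2 = 6. The two day-14 outcomes are affected only if the patient has not yet reached them.
- The course of the triggering event and any later event.

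**4. What is probably not lost**

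- The percentage of participants with adverse events: the patient is already counted.
- The day-7 primary outcome: it is lost only if observation ends before improvement is recorded. Section {11c} says all participants are inpatients managed by the research doctor, so status may still be available for those still admitted.

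**5. How many patients**

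This cannot be derived. The article gives no rate of persisting mild or moderate events in either arm. The number is 0 if every site keeps assessing after it acts on the rule.

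**The case against.** The strongest reply is that this is one loosely worded sentence. It does not say that visits or data collection stop, and Table 2 marks the later assessments as mandatory. The ITT population keeps every randomised patient, and early stopping does not by itself remove anyone from the mITT population. Multiple imputation is planned. A condensed article may also leave follow-up after discontinuation to the full protocol.

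Much of this stands. Loss of observation is a risk that the wording creates, not a stated consequence, and the analysis populations are not the problem. Two things remain. The point concerns an order that the article does state, not detail that it omits. And imputation can supply values for missing outcomes under assumptions, but it does not recover how an adverse event ran.

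A reader might infer three stronger points, which the document does not support:

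- *A site doctor could stop the whole study and override the DMC.* The sentence concerns patients and site doctors, and the DMC's own task is only "making recommendations to continue or terminate the study". This is an ambiguity of wording, not a conflict of authority.
- *The rule contradicts Table 3 for mild events*, where it says "Participants can continue to participate in the trial without medical treatment and impact on the health". That line describes how an event is graded. By the same table, an event that needs treatment or is not tolerated is already moderate, so the overlap is nearly empty: it is reached mainly when the dose was reduced for a mild event.
- *The rule breaches the retention section*, which has investigators stress "continuing to retain and complete the trial, including better observation of drug efficacy and potential adverse reactions". That text addresses patients who themselves ask to withdraw, not a stop for safety.

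**Conclusion.** The point holds as a minor one. The order exceeds what is needed to protect a patient with a persisting event that is not life-threatening, and it applies whatever the cause. Followed literally, it can cost that patient up to 3 visits and 21 of 28 days, and with them data on up to six secondary outcomes and the course of the event.

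This rests on two assumptions: that some sites would read the order as ending participation, and that they would then stop assessing. An imbalance between arms further assumes that the anticipated herbal reactions persist more often on QZQG. The article says only that such reactions may occur and gives no rate. Damage to the primary outcome is possible but less likely, and the point does not depend on it.

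**What to change.** In Assessment of adverse events, keep the ethics report for both mild and moderate events and replace the termination order with: *discontinue study drug for that participant, with all scheduled outcome and safety assessments continuing to day 28 unless consent is withdrawn*. The word mild need not be deleted; deleting it would also remove the ethics report for a persisting mild event.

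The cost is one protocol wording change and site retraining. No visits are added, because days 14, 21 and 28, with adverse-event recording, are already in Table 2.
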